**LIST OF ABBREVIATIONS**

| AE | Adverse Event |
| --- | --- |
| AR | Adverse Reaction |
| BSIR | British Society of Interventional Radiology |
| CDMS | Clinical Data Management System |
| CI | Chief Investigator |
| CLTI | Chronic Limb-Threatening Ischemia |
| CRF | Case Report Form |
| CTU | Clinical Trials Unit |
| GCP | Good Clinical Practice |
| ICF | Informed Consent Form |
| ISF | Investigator Site File |
| JLA | James Lind Alliance |
| LCTU | Leicester Clinical Trials Unit |
| MDT | Multi-Disciplinary Team |
| NHS R&D | National Health Service Research & Development |
| PAD | Peripheral Arterial Disease |
| PI | Principal Investigator |
| PIC | Participant Identification Centre |
| PIS | Participant Information Sheet |
| QC | Quality Control |
| QRI | QuinteT Recruitment Intervention |
| RFS | Research Filestore Service |
| RCT | Randomised Control Trial |
| REC | Research Ethics Committee |
| SAE | Serious Adverse Event |
| SAR | Serious Adverse Reaction |
| SEAR | Screened, Eligible Assess, Randomised |
| SOP | Standard Operating Procedure |
| TASC | Trans-Atlantic Inter-Society Consensus |
| TMF | Trial Master File |
| TMG | Trial Management Group |
| TSC | Trial Steering Committee |
| VSGBI | Vascular Society of Great Britain and Ireland |

**KEY WORDS**

Peripheral arterial disease, endovascular, vascular

**TRIAL SUMMARY**

| **Trial Title** | A randomised controlled trial assessing the clinical and cost-effectiveness of Endovascular vs. Open revascularisation in severe oCClusive aorto-iliac disease. (**EVOCC)** | |
| --- | --- | --- |
| **Trial Design** | A parallel group, multicentre, prospective, open label, randomised controlled trial (with an internal pilot) of endovascular vs. open revascularisation in patients with severe oCClusive aorto-iliac disease. | |
| **Participating Sites:** | Over 30 NHS hospital sites in the UK (England, Scotland and Wales) | |
| **Trial Participants** | Adult patients with symptomatic peripheral arterial disease who have severe aorto-iliac occlusive disease (TASC II class C or D) and are undergoing revascularisation of their aorta/iliac arteries | |
| **Planned Sample Size** | 628 | |
| **Recruitment Period** | 6 month pilot recruitment phase and 24 months for the main recruitment phase. | |
| **Follow Up Duration** | Minimum 2 years (maximum 4.5 years, median 3 years) | |
| **Planned Trial Period** | **Grant start date**: 01/01/2023  Total grant duration 69 months, including 6 month pilot recruitment, 24 months main recruitment and 24 months of patient follow-up. | |
|  | **Objectives** | **Outcome Measures** |
| **Primary** | Establish whether the clinical and cost-effectiveness of open surgery for severe occlusive aorto-iliac disease (TASC II C/D) is superior to endovascular treatment? | Combined measure of death or major lower limb amputation, measured in days from randomisation until first event or until the end of the trial (minimum 2 years) where no event occurs |
| **Secondary** | (i) Identify whether open surgery for severe occlusive aorto-iliac disease is superior to endovascular treatment in terms of amputation-free survival with median 3 year follow-up (minimum 2 years).  (ii) Establish the cost-effectiveness of the interventions including differences in quality-of-life of patients. | (i) Mortality (all cause)  (ii) Cardiovascular events  (iii) Hospital admissions (incl. reason for admission)  (iv) Re-interventions (incl. nature of re-intervention)  (v) All lower limb amputations (minor and major i.e. below and above ankle joint) all measured as time until first event as described for the primary outcome  (vi) Concomitant medications  (vii) Estimated glomerular filtration rate (renal function) based on serum creatinine levels using the Chronic Kidney Disease Epidemiology (CKD-EPI) formula  (viii) Low Density Lipoprotein (LDL)  (ix) HbA1C  (x) Cholesterol  (xi) Ankle Brachial Pressure index (ABPI)  (xii) Details of intervention  (xiii) Quality-of-life using the EQ-5D-5L questionnaire  (xiv) Healthcare resource use and costs across follow-up assessments over a minimum of 24 months |

**ROLE OF TRIAL SPONSOR**

The study has been funded by a grant from the NIHR Health Technology Assessment (HTA) Programme (ref: NIHR151230). Additional support and resources for the study will be provided by the participating Trusts and their corresponding Clinical Research Networks (CRN). The funder will be responsible for funding the study but will not be part of the study conduct, data analysis and interpretation, manuscript writing, and dissemination of results.

The Sponsor, the University of Leicester, will be responsible for all aspects of the study. The Sponsor will delegate duties to other parties, including Leicester Clinical Trials Unit (LCTU), this delegation will be formally documented. However, like the funder, the Sponsor will not be part of the study conduct, data analysis and interpretation, manuscript writing, and dissemination of results.

**TRIAL FLOW CHART**

Setting NHS Hospitals providing specialist care to patients with PAD

Patients with severe occlusive aorto-iliac PAD presenting with symptomatic peripheral arterial disease [rest pain and/or tissue loss (gangrene) and/or life style limiting claudication], already being considered for revascularisation

Screening & enrolment

**Inclusion criteria:** patient deemed eligible for both open & endovascular procedure

**Exclusion criteria:** Age ≤18 years, Asymptomatic PAD

**Randomisation**

**Discussion at vascular meeting**

**Informed consent**

Allocation 1:1

Follow-up

**Open surgery**

314 participants

(With or without inflow/outflow procedures)

**Endovascular treatment**

314 participants

(With or without inflow/outflow procedures)

2-year minimum follow-up including assessments for death, amputation, any subsequent operation, cardiovascular events and quality-of-life (validated questionnaire)

Analysis

Primary outcome of interest: death and/or major lower limb amputation (amputation free survival)

Analysis of clinical & cost-effectiveness

**Internal pilot:**

6 months

10 sites (nationally)

**Main recruitment period:**

24 months

Over 30 sites (nationally)

628 participants

**Figure 1. EVOCC CONSORT diagram**

Figure 1

# BACKGROUND

The clinical and cost-effectiveness of open surgery vs. minimally invasive endovascular treatment for severe occlusive aortic and iliac artery disease is unknown. This area has been identified as a research priority in a recent James Lind Alliance (JLA) process across several vascular disease areas, such as peripheral arterial disease (PAD), diabetic foot care, and amputations (1).

Lower limb Peripheral Arterial Disease (PAD) affects 20% of people over 55 years of age (2) and is the main cause of amputations in the NHS (2). Often, patients with PAD develop leg pain when walking (called claudication). Some patients might also develop leg pain at rest or lower limb necrosis, a condition called Chronic Limb Threatening Ischaemia (CLTI) (3). This is limb and life threatening and requires urgent revascularisation to save the patient’s limb/life (3). The aorta and iliac arteries are common sites affected in people with lifestyle limiting claudication or CLTI (4). These patients can have revascularisation either with open surgery or more recently developed minimally invasive techniques in the form of endovascular treatment (3). Both open surgery and endovascular treatment, however, are associated with significant complications. Open surgery is associated with a 3% early mortality and many perioperative complications (5). Endovascular treatment is less invasive, with a 1% early mortality rate (5, 6). Endovascular devices, however, are costly and 43% of patients need re-intervention within 3 years (5).

Patients in our study development focus groups expressed a preference for endovascular treatment. They were, however, concerned about the many re-interventions and high number of late deaths or amputations potentially associated with endovascular treatment. Some patients even voiced concerns about the high cost of the endovascular devices and many re-interventions. There is no randomised evidence comparing the clinical and cost-effectiveness of these techniques in this context, potentially leading to more deaths, amputations, and increased NHS costs. Clinicians therefore do not know which treatment to offer this cohort. The need to improve outcomes and reduce amputations in CLTI/claudication has been highlighted by the JLA and Vascular Society of Great Britain and Ireland (VSGBI) in 2021 as a key research priority (1).

# RATIONALE

There is no randomised evidence comparing the clinical and cost-effectiveness of open or endovascular interventions to address severe occlusive aorto-iliac disease, which creates great uncertainty for patients with PAD and clinicians. It also leads to an estimated 7,000 excess deaths and amputations, and £180 million in excess NHS costs per year, based on our published evidence and HES data (6, 7). The need to improve outcomes and reduce amputations in this group of patients has been highlighted by the JLA in 2021 as an urgent research priority (1).

## Healthcare need and clinical effectiveness

An international multidisciplinary expert group in PAD, the Trans-Atlantic Inter-Society Consensus (TASC) force, classified aorto-iliac PAD based on severity of arterial stenoses or occlusions from grade A (less severe) to grade D (most severe) (1). For TASC A/B disease (1), endovascular treatment is the universally established and accepted strategy both in the NHS and globally (1). For TASC C/D disease, there is great uncertainty regarding the effectiveness of open surgery vs. endovascular treatment, reflected in all guidelines (1). The fact that endovascular therapies (stents, angioplasties, other endovascular procedures) have seen great advances in the last 20 years has added even more uncertainty regarding the management of patients with TASC C/D aorto-iliac PAD. Clinicians and patients do not know whether surgery or endovascular treatment, especially with the newer devices now available across the NHS as routine care, are better in terms of saving lives, legs, and improving quality of life.

[figure not shown]

**Figure 2.** TASC classification for patients with aorto-iliac arterial disease. TASC C and D patients have severe occlusive disease and are more likely to present with severe symptoms; these patients will be eligible to take part in EVOCC as there is treatment uncertainty in this group regarding superiority of surgery over newer endovascular (minimally invasive) treatment.

## Economic impact and cost effectiveness

We obtained information from our published meta-analysis (1) and HES to identify patients with CLTI/claudication and TASC C/D aorto-iliac disease who had revascularisation between 2014-2019. We then constructed an early decision model to calculate 3 year death, amputation, and re-intervention rates, NHS resource use, and quality-adjusted life years (QALYs). Open surgery is associated with a peri-operative mortality of 3% vs. 1% for endovascular treatment. The latter is associated with more re-interventions and late amputations/deaths. Three year survival is 70% for open surgery vs. 65% for endovascular treatment (HES data). Open surgery costs arise from intensive care stay and early complications. Endovascular treatment costs arise from devices, re-interventions, and late amputations. Average peri-operative and device costs are £13,765 for endovascular treatment. Late re-interventions and amputations cost £6,811, totalling £20,576 for endovascular treatment over 3 years. Open surgery costs £10,675 over 3 years (£9,901 less per patient). The 3 year QALY difference is 0.153, favouring open surgery, despite the higher immediate mortality/morbidity. All of these estimates, however, are based on unadjusted observational data. Overall, it is very uncertain whether endovascular treatment, despite being minimally invasive, is cost-effective in the NHS.

## Sustained interest and intent

PAD is very common, especially in those with diabetes, socioeconomically deprived populations, South Asian, Afro Caribbean, and Eastern European minorities (1), with increasing prevalence nationally (2,3). Symptomatic PAD, mostly in the form of CLTI or lifestyle limiting claudication, accounts for 75% of the current NHS vascular workload based on HES, the National Vascular Registry, and cohort studies (1). The number of amputations due to PAD is rising, especially in those with diabetes (1).

## Capacity to generate new knowledge

This will be the first randomised trial assessing clinical and cost-effectiveness in this clinical context worldwide.

## Evidence and literature

We published a meta-analysis of 66 observational studies (9,319 patients) (1) and a cohort study of patients having aorto-iliac endovascular treatment across multiple NHS hospitals (1). We also identified all patients who had surgery or endovascular treatment (2014 to 2019) for TASC C/D aorto-iliac disease using HES and recorded 3 year outcomes. We performed an audit in 7 NHS hospitals to identify how many patients treated for TASC C/D aorto-iliac disease are eligible for randomisation. We have searched all trial repositories including the WHO trials registry in December 2021 (updated April 2022). Main findings:

- There are no relevant completed or ongoing trials; a recently completed trial in a similar context did not include all-comers and aorto-iliac disease, but only selected patients with iliac and common femoral artery disease, treated with a combination of open surgery and endovascular devices (1)
- Between 2014-2019, an average 2,200 patients per year received open surgery for these indications and 6,800 received endovascular treatment in the NHS (HES)
- Peri-operative mortality in observational series and HES, not adjusted for co-morbidities or anatomical complexity, was 3% for open surgery vs. 1% for endovascular treatment; 43% of those having endovascular treatment required re-intervention within 3 years
- In the meta-analysis, we observed significant bias favouring publication of studies with positive outcomes
- In the audit of 7 NHS centres, 82% of patients with TASC C/D disease would be eligible for randomisation in EVOCC
- No relevant PPI initiatives were identified in the literature
- Healthcare professionals’ views on equipoise had not been explored.

## Evidence supporting the need for the trial and study design based on PPI and staff views

Three patient focus groups were convened to develop EVOCC. Eleven patients who had endovascular treatment, 7 who had open surgery, 3 carers, and 4 partners took part, from multiple ethnic and socioeconomic backgrounds. Most patients had diabetes and 5 previously had a leg amputation. We explored outcomes of interest, follow-up procedures, study acceptability, and clinically important differences. All agreed that the main outcome measure should include mortality and amputations (equally weighted), which are the two things that matter most to patients. They specifically supported that follow-up should continue for a minimum of 2 years. Patients reported that they keep needing re-interventions or amputations several months after surgery and/or endovascular treatment. All would take part in the study and found randomisation acceptable. When asked, they supported a superiority design of surgery vs. endovascular treatment. Patients would like to know whether the more invasive option (surgery) is better at saving legs and lives vs. the least invasive treatment. These patients have reviewed and approved the study design.

To explore equipoise amongst healthcare staff nationally, we performed a survey of 60 surgeons, 23 radiologists, and 8 nurses. This covered 38 NHS sites (64% of all UK vascular centres). Overall, 97% agreed this trial is necessary; 88% felt it would be possible to deliver within a 2 year main recruitment period. Finally, 91% of surgeons and radiologists felt they were in equipoise and would recruit/randomise patients.

# RESEARCH QUESTION, OBJECTIVES AND OUTCOME MEASURES

## Research question

Is the clinical and cost-effectiveness of open surgery for severe occlusive disease of the aorta and iliac arteries superior to newer endovascular (keyhole) treatment?

## Primary objective

To identify whether the clinical and cost-effectiveness of open surgery for severe occlusive disease (TASC II C/D) of the aorta and iliac arteries is superior to endovascular treatment.

## Secondary objectives

- Identify whether open surgery for severe occlusive aorto-iliac disease is superior to endovascular treatment in terms of amputation-free survival (death and/or major lower limb amputation) over a minimum 2 year follow-up period (median 3 years).
- Establish the cost-effectiveness of the two interventions, including quality-of-life differences.

## Exploratory objective

To identify any association between the use of different endovascular techniques or open surgical configuration and subsequent primary outcome (amputation free survival).

# Outcome measures

## Primary outcome

Combined measure of death or major lower limb amputation, measured in days from randomisation until first event or until the end of the trial (minimum 2 years) where no event occurs.

## Secondary outcomes

Secondary outcome measures are:

1. Mortality (all cause), measured in days from randomisation until first event or until the end of the trial (minimum 2 years) where no event occurs
2. Cardiovascular events (myocardial infarction, stroke, admission for heart failure), measured in days from randomisation until first event or until the end of the trial (minimum 2 years) where no event occurs
3. Number of hospital admissions (including reasons for readmissions), following discharge from index surgical admission for up to 4.5 years
4. Number of re-interventions (including nature of re-intervention), following index surgical procedure for up to 4.5 years
5. All lower limb amputations (minor and major i.e. below and above ankle joint) measured in days from randomisation until first event or until the end of the trial (minimum 2 years) where no event occurs
6. Concomitant medications (specifically: use of statin, use of antithrombotic medication)
7. Estimated glomerular filtration rate (renal function) based on serum creatinine levels using the Chronic Kidney Disease Epidemiology (CKD-EPI) formula measured at 6 and 12 months and annually thereafter
8. Low Density Lipoprotein measured at 6 months
9. HbA1C measured at 6 months
10. Cholesterol measured at 6 months
11. Ankle Brachial Pressure Index (ABPI) measured at 6 and 12 months and annually thereafter
12. Types of endovascular devices used and/or name of surgery performed (open)
13. Quality-of-life using the EQ-5D-5L measured at 6 and 12 months and annually thereafter
14. Healthcare resource use and costs measured across follow-up assessments over a minimum of 24 months and until the end of the trial

A prospectively planned economic evaluation will be conducted from an NHS and personal social services perspective as per NICE recommendations.

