## Trial assessments

### Baseline Visit (Day 0)

Once a Participant ID Number is allocated, the Baseline visit can take place. During this visit, participants will complete participant questionnaires, undergo a review of their medical history (including previous surgical interventions), cardiovascular risk factors, PAD anatomy, eGFR, HbA1C, LDL and cholesterol levels. If a female is thought to be pregnant, a urine pregnancy test will be performed as part of usual care ahead of surgery. Where a female participant is found to be pregnant, progression to treatment will be assessed using a risk-based approach as managed routinely by the patient’s treating clinician. Baseline visit biochemistry assessments/bloods to be taken in line with clinical pathway and matching the research schedule as closely as possible. It is understood that because these bloods are clinical, that there may be occasions where these bloods are taken ahead of the research baseline timepoint. Please refer to **Table 2** for further details about the Baseline visit, follow up visits and assessments.

### Review of Clinical Events – Day of Discharge, Day 30 and Months 6, 12, 24, 36, 48 and 54

A review of clinical events, particularly those related to the cardiovascular system, will be undertaken at the above trial visits including re-intervention, admission to hospital, death, myocardial infarction, stroke and new heart failure leading to admission. For visits at day 30, months 12, 36, 48 and 54, data collection will be performed either by telephoning the participant or retrieving the information from their medical notes. For visit month 6, the participant needs to attend clinic in person. However, if the participant cannot attend in person, as this is a pragmatic study this information can instead be collected remotely via telephone or through acquiring information through participant medical records.

### Biochemistry Assessments – Baseline and Month 6

Standard blood sample assessments to be undertaken in clinic at Baseline and month 6 and should include eGFR, total cholesterol, LDL cholesterol and HbA1C - these are NHS standard of care and constitute part of these patients regular care as per NHS and National Institute for Health and Care Excellence guidance. The blood samples (5ml collected at each visit) will be collected at room temperature before being processed and analysed at the local pathology laboratories as per each site’s standard procedures for these patients.

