**Table 2. Schedule of Assessments**

| **VISIT** | **Time points** | | | | | | | | | |
| --- | --- | --- | --- | --- | --- | --- | --- | --- | --- | --- |
|  | **Baseline** | **Trial intervention** | **Day of Discharge** | **30 Days** | **6 months** | **12 months** | **24 months** | **36 months^1^** | **48 months^1^** | **54 months^1^** |
| **Visit window (days)**  (± number of days this visit can take place ahead or after its due date) | - | **-** | **-** | ± 7 days | ± 30days | ± 30 days | ± 30 days | ± 30 days | ± 30 days | ± 30 days |
| **Day** | 0 |  |  | 30 | 180 | 365 | 730 | 1095 | 1460 | 1643 |
| Eligibility check | x |  |  |  |  |  |  |  |  |  |
| Obtain informed consent | x |  |  |  |  |  |  |  |  |  |
| Randomisation (allocation of treatment) | x |  |  |  |  |  |  |  |  |  |
| Demographics | x |  |  |  |  |  |  |  |  |  |
| Medical history including cardiovascular risk factors | x |  |  |  | x |  |  |  |  |  |
| Details of anatomy (arteries) | x |  |  |  |  |  |  |  |  |  |
| Concomitant medications (statins and antithrombotics) | x |  | x | x | x | x | x | x | x | x |
| Review of clinical events |  |  | x | x | x | x | x | x | x | x |
| Days lost from regular activities |  |  |  |  | x | x | x | x | x | x |
| Estimated Glomerular Filtration Rate (eGFR) | x |  |  |  | x |  |  |  |  |  |
| Low Density Lipoprotein (LDL) value | x |  |  |  | x |  |  |  |  |  |
| Total Cholesterol value | x |  |  |  | x |  |  |  |  |  |
| HbA1C value | x |  |  |  | x |  |  |  |  |  |
| Ankle Brachial Pressure Index (ABPI) | x |  |  |  | x | x | x | x | x | x |
| EQ-5D-5L questionnaire | x |  |  |  | x | x | x | x | x | x |
| Details of intervention (type of surgery or endovascular treatment configuration and devices) |  | x |  |  |  |  |  |  |  |  |
| Admission to hospital or visit to primary care |  |  |  |  | x | x | x | x | x | x |
| Assessment of Adverse Events | x | x | x | x | x | x | x | x | x | x |

^1^ The follow up trial visitsmay be undertaken remotely either via telephone or through acquiring information through participant medical records. For 6 months, in the first instance please try to bring the patient in for a face-to-face appointment. If this is not possible then this follow-up visit may also be undertaken remotely via telephone or through acquiring information through participant medical records.

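### eGFR is defined as a secondary outcome at months 6, 12 and yearly after that, but section 8.4.3 and Table 2 schedule it only at baseline and month 6

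*Protocol*

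**What the plan says.** Item 7 of section 4.2 (Secondary outcomes) sets the timing of eGFR: "using the Chronic Kidney Disease Epidemiology (CKD-EPI) formula measured at 6 and 12 months and annually thereafter".

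Section 8.4.3, headed "Biochemistry Assessments – Baseline and Month 6", sets the blood sampling: "Standard blood sample assessments to be undertaken in clinic at Baseline and month 6 and should include eGFR". Table 2 agrees with section 8.4.3. Its eGFR row reads "Estimated Glomerular Filtration Rate (eGFR) | x | | | | x", which places marks under baseline and 6 months, and the columns for 12 to 54 months are empty.

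The neighbouring outcomes are a useful comparison. Item 8 is "Low Density Lipoprotein measured at 6 months", and HbA1c and cholesterol are timed in the same way. Item 11 is "Ankle Brachial Pressure Index (ABPI) measured at 6 and 12 months and annually thereafter", the same timing as eGFR, and its Table 2 row is "Ankle Brachial Pressure Index (ABPI) | x | | | | x | x | x | x | x | x".

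Section 8.5 allows follow-up from month 12 by telephone or from medical records. Section 8.4.3 describes the bloods as standard NHS care.

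**The concern.** The outcome list and the assessment schedule disagree about when eGFR is measured. Sites work from the schedule, so the data will follow Table 2 unless the text is changed. The trial would then hold one follow-up eGFR value per participant for an outcome that was specified as repeated over the whole of follow-up.

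This leaves an awkward choice at reporting. Presenting month 6 alone departs from the outcome definition. Filling in later points from whatever the notes contain departs from the schedule, and no rule says which results to take. An analysis plan cannot settle this on its own, because it cannot analyse values that sites were never asked to record. eGFR is also the only renal function measure among the 14 secondary outcomes.

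**Working it through.** The protocol states no figure to reproduce here. The check compares the defined time points with the scheduled ones.

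**Step 1. Definition against schedule**

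| Measure (section 4.2 item) | Defined follow-up timing | Table 2 follow-up marks (months) | Agree? |
|---|---|---|---|
| eGFR (7) | 6, 12, then yearly | 6 | No |
| LDL (8), HbA1c (9), cholesterol (10) | 6 | 6 | Yes |
| ABPI (11), EQ-5D-5L (13) | 6, 12, then yearly | 6, 12, 24, 36, 48, 54 | Yes, with month 54 in addition |

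The ABPI and EQ-5D-5L rows carry marks out to month 54, so the empty cells in the eGFR row are not a fault of text extraction. eGFR is the only one of these measures whose Table 2 row falls short of its definition. (The heading of section 8.4.5 names fewer EQ-5D-5L visits than Table 2. That is a separate matter.)

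**Step 2. Count of points**

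- The trial summary gives a maximum follow-up of 4.5 years, which is 54 months.
- Month 6 plus the yearly points up to 54 months gives 6, 12, 24, 36 and 48, so five points are defined.
- Scheduled: month 6. Not scheduled: 12, 24, 36 and 48, which is 5 − 1 = 4 of 5.
- Within the minimum 24 months, the defined points are 6, 12 and 24. Not scheduled: 3 − 1 = 2 of 3.

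**Step 3. How many participants each point concerns**

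Assumptions: 30 months of accrual (6 pilot plus 24 main), a common end at month 54 from the first recruit, and no deaths or losses. A participant reaches month *m* if recruited by month 54 − *m*.

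- Months 6, 12 and 24: 100%.
- Month 36 (recruited by month 18): 18/30 = 60% under uniform accrual. With 60 recruited in the pilot and 568 spread evenly over the main phase, (60 + 568 × 12/24)/628 = 344/628 = 55%.
- Month 48 (recruited by month 6): 6/30 = 20%, or 60/628 = 10%.
- Month 54: about 0%.

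Defined points per participant: 1 + 1 + 1 + 0.60 + 0.20 = 3.8, or 1 + 1 + 1 + 0.548 + 0.096 = 3.6. Scheduled: 1. Most of the shortfall is at months 12 and 24.

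**The case against.** The case for leaving this alone, or treating it as trivial, is that it affects one of 14 secondary outcomes and touches neither the primary outcome nor the power. The bloods are described as routine care, and later visits may use medical records. Acute kidney injury and transient renal replacement therapy are on the section 9.1 list of expected events that go on the routine follow-up CRFs. The limited reach is accepted. The rest does not remove the contradiction: permission to use records for follow-up is not an instruction to extract creatinine, and event reports are not eGFR values.

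The objection does succeed against four stronger readings that a reader might infer.

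- *Five of six points are missing.* This needs month 54, which is not a yearly point. It appears in Table 2 for other measures but not in the wording of item 7.
- *The later values will not exist.* The protocol supports only the statement that their collection is not scheduled. Some may be in the notes.
- *Values taken from the notes would be biased because only ill participants are tested.* The protocol does not say this, nor does it propose filling the gap this way. Selective testing is plausible, but it is an assumption.
- *The planned analysis cannot be run.* Section 11.6 reserves mixed models for outcomes repeated over time and allows linear regression for continuous outcomes, so a single follow-up value already has a method.

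**Conclusion.** The point holds as an internal inconsistency. Item 7 of section 4.2 conflicts with both section 8.4.3 and Table 2, and nothing else in the protocol resolves it. Four of the five defined eGFR follow-up points are unscheduled, two of the three within minimum follow-up, so the outcome cannot be reported as defined.

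The count rests on a literal reading of yearly up to 54 months. The 55–60% and 10–20% shares at months 36 and 48 rest on the accrual assumptions stated above and serve only to show where the gap falls. The consequence is confined to one secondary outcome, but it is worth correcting because the later values depend on sites being told to collect them.

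**What to change.** Reconcile the sections by amendment, in one of two ways.

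1. Restate item 7 as eGFR at month 6 only, as for LDL, HbA1c and cholesterol. Analyse it by linear regression adjusted for baseline eGFR, alongside the adjustment that section 11.6 already calls for. The cost is one line in section 4.2. It narrows a pre-specified outcome, so the amendment history should say so.
2. Keep the longer definition and add eGFR to the Table 2 visits from month 12, by recording the latest routine creatinine and its date from the notes. Section 8.4.3 would be edited to match. The cost is one extra records-based item at visits that already exist. Recording the date lets the analysis show how far each result lies from its visit and how many participants have none, so that any selectivity can be seen.

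The trial summary lists eGFR without time points and can stay as it is.
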